### Procedure

Patients will be stratified by rehabilitation centre and subsequently randomized to task-oriented CCT or to individual face-to-face physiotherapy, using an 'online' minimization procedure[27]. The intervention period will be 12 weeks and measurements will be taken at baseline, 6, 12, 18 and 24 weeks. All outcomes measured at baseline, 12 and 24 weeks will be assessed in face-to-face meetings by an independent researcher, blinded for treatment allocation, whereas at 6 and 18 weeks, a restricted set from the test battery will be assessed by semi-structured telephone interviews (Figure 1).

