### Participants

Eligible subjects will have to meet the following inclusion criteria: (1) verified stroke according to the WHO definition[23], (2) ability to walk a minimum of 10 m without physical assistance from a therapist. (i.e., patient may require verbal supervision or stand-by help from a person, and using an aid or orthotics is allowed) (Functional Ambulation Categories ≥ 3); (3) discharged home from a rehabilitation centre; (4) need to continue physiotherapy during outpatient care to improve walking competency and/or physical condition; (5) giving informed consent and being motivated to participate in 24 fitness training sessions over a 12-week period, or in usual care. Patients will be excluded if they (1) suffer from severe cognitive deficits as evaluated by the Mini-Mental State Examination (<24 points); (2) are unable to communicate (i.e. < 4 points on the Utrechts Communicatie Onderzoek) or (3) live more than 30 km from the rehabilitation centre. Before discharge from an inpatient rehabilitation setting, patients will be recruited by their own physician, and after they have given written informed consent, an observer will verify if all inclusion criteria have been met to participate in the trial. The FIT-Stroke protocol has been approved by the Medical Ethics Committee of the University Medical Centre Utrecht and all the participating rehabilitation centres. The trial is registered in the Dutch Trial Register (NTR1534).

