### Compliance

In order to conduct this trial uniformly in nine different rehabilitation centres, all supervisors have to be trained in a one-day course before the FIT-Stroke trial starts. In the past year, about 60 physiotherapist and sports therapists have been trained. Each therapist has been informed about: (1) the criteria for recruitment of candidates discharged from the inpatient rehabilitation centre; (2) the aims, design and measurement instruments of the FIT-stroke trial, (3) how to fill in the patients' training diaries, (4) the focus and content of the task-oriented CCT programme and (5) how to stimulate the participants to maintain an active lifestyle after the task-oriented CCT sessions end. After practical training about applying and adapting the eight workstations and how to intensify the workload progressively, all trained supervisors were able to conduct the intervention in a standardized manner. Subsequently, all other physiotherapists, sports therapists and physicians who will be involved in the treatment of the included stroke patients were informed about the content of the intervention by means of presentations in each rehabilitation centre. In order to prevent contamination, therapists were instructed not to change the treatment procedures of the usual face-to-face physiotherapy during the trial. Finally, all managers of rehabilitation centres were asked not to change treatment policies during the FIT-Stroke trial. In the coming years, retraining activities will be organized and an independent investigator ([name]) will monitor on a regular basis whether the content of the task-oriented CCT and the usual physiotherapy are being implemented as intended in the nine rehabilitation centres.

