### Power analysis

A difference of 5 points (about 11%) on the 'mobility at home and in the community' domain of the SIS in favour of the experimental group will be regarded as clinically relevant[33], whereas the standard deviation for this population is estimated at a maximum of 14 points (28%) based on 287 mild and moderate SIS responses[55]. In addition, test-retest reliability (ICC) is known to be about 0.8[33], whereas the FIT-Stroke trial uses 4 repeated measurements in the first 24 weeks after randomization. Therefore, a minimum of 99 patients will be required for each arm of the trial. Expecting a dropout rate of 10%, we assume that a minimum of 220 stroke patients will be needed to achieve a sufficient statistical power of 80%.

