## Discussion

The FIT-Stroke trial is a single-blinded multicentre trial in which 220 patients will be allocated to task-oriented CCT or usual face-to-face treatment at the nine participating rehabilitation centres, on the basis of a minimization procedure. The minimization procedure used for patient allocation has been recommended as a highly effective allocation method for randomized controlled trials[27].

The main characteristics of the task-oriented CCT programme are the progressive intensity and task specificity of the workstations used. The eight different functional workstations used in the trial have been found to be meaningful and relevant to patients' needs, goal-oriented, challenging, and feasible (i.e., not to easy and not to difficult). As such, the programme builds heavily on the existing evidence that intensity of practice[12,57] as well as task specificity[13,57] are the main drivers of gait improvement. After reviewing 14 trials, French and colleagues[13] showed that repetitive task-oriented training resulted in modest improvement in lower limb function. Although the authors claimed that the repetitive lower limb training was sufficient to influence daily living functions, no evidence was found that the effects of repetitive training were sustained once training had ended. In order to fill this gap in existing evidence, the FIT-Stroke trial will have a follow-up of three months to investigate the possible wash-out effects of the task-oriented CCT programme.

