Recently, Wevers and colleagues showed significant effects in favour of task-oriented CCT for walking distance, gait speed and a timed up-and-go test in their systematic review of randomized controlled trials including 307 participants[19]. The intensity of task-oriented CCT ranged from 4 weeks (3 times a week for 60 minutes)[24] to 19 weeks (3 times a week for 60 minutes)[58]. Therefore, we assume that in the present study, a training schedule of 24 sessions each lasting 90 minutes within 12 weeks will be sufficient to achieve functional gains in gait and gait-related activities. Unfortunately, most studies included in the above meta-analysis were small and statistically underpowered, ranging from 12[24] to 91[59] participants, which suggests that larger trials are warranted. Only one study[60] included in the meta-analysis investigated the effects of task-oriented CCT within the first 6 months post stroke. Interestingly, this study found a larger effect size than those that investigated effects in chronic stroke. However, none of the included studies compared the cost-effectiveness of task-oriented CCT with that of usual care, which is particularly important in view of the burden of health care costs for stroke and attempts to save costs in stroke management. This aim is in line with the views of the American Hearth Association (AHA), which recently recommended that fundraisers and researchers should conduct cost-effectiveness studies in the growing and ageing stroke population[8]. By including 220 patients within the first months after their stroke and focusing on cost-effectiveness as well as health-related quality of life, we hope to fill the existing gaps in stroke rehabilitation research.

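### Centre is the only balancing factor named, yet the covariate rule could drop centre and baseline FAC from the random coefficients model; both should be entered in advance

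*Protocol article*

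**What the plan says.** All references are to the protocol article.

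- **Allocation.** Procedure states: "Patients will be stratified by rehabilitation centre and subsequently randomized to task-oriented CCT or to individual face-to-face physiotherapy", by an online minimisation procedure for which a reference is cited. Design adds that allocation takes place within each centre. The Discussion says again that patients are allocated "on the basis of a minimization procedure". No section names a balancing factor other than centre, and none gives an assignment probability.
- **Analysis.** Data analysis specifies a random coefficients model with repeated measurements nested in patients. Besides treatment arm, it admits factors found significant in univariate regression. Neither centre nor FAC is named as a covariate, and centre is not named as a level of the model.
- **FAC.** Baseline walking level is collected. It is an eligibility threshold (3 or higher) and a secondary outcome.
- **Recruitment and blinding.** Under Participants, "patients will be recruited by their own physician"; consent follows, and an observer then checks eligibility. The outcome assessor is the only person stated to be blinded.
- **Size.** Power analysis says that "a minimum of 99 patients will be required for each arm of the trial", which implies equal arms. The total is 220 after 10% dropout.

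**The concern.** A factor used to balance the arms should be in the model. Balancing removes the variation between arms that is due to that factor. A model without the factor still counts that variation as noise between patients, so the standard error is too large and the test is conservative. The precision bought by the design is then lost in the analysis.

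Baseline FAC is a different case, because the article does not name it as balanced. A measured baseline walking level is an obvious candidate to predict a patient-reported mobility score. Entering it in advance gains precision and deals with chance imbalance.

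Under a significance rule, neither adjustment is known before the outcome data are seen.

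A second, conditional matter is predictability. With centre as the sole factor and no random element, anyone who can count a centre's earlier allocations knows the next arm whenever the two counts differ. Choice of patient or timing of entry could then depend on the arm. Blinding the assessor would not correct that.

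**Working it through.** **1. Planned size.** Inputs from Power analysis: difference 5, SD 14, ICC 0.8, power 80%, dropout 10%. The significance level is not stated; 5% two-sided is assumed.
- 2 × (14 × (1.960 + 0.842) / 5)² = 123.1 per arm
- 123.1 × 0.8 = 98.5, so 99
- 99 / 0.9 = 110 per arm, 220 in total

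The article's figures reproduce. Only the 220 and the nine centres are used below.

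**2. Cost of leaving centre out.** Let R² be the share of between-patient outcome variance explained by centre. With arms balanced within centre, the true variance of the treatment difference is proportional to 1 − R², but the model without centre estimates it as proportional to 1. The reported standard error is too large by the factor 1/√(1 − R²). The true size of a nominal 5% test is 2 × [1 − Φ(1.96/√(1 − R²))].

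The chance that centre fails a 5% univariate F test (8 and 211 degrees of freedom, critical value 1.98) comes from the noncentral F distribution with noncentrality 220 × R²/(1 − R²). The article gives neither R² nor the screening level, so these are assumptions shown as a range, with one outcome value per patient and no missing data.

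| Assumed R² | SE factor if omitted | True test size | Noncentrality | Chance centre is dropped |
|---|---|---|---|---|
| 0.02 | 1.010 | 4.8% | 4.5 | 74% |
| 0.05 | 1.026 | 4.4% | 11.6 | 35% |
| 0.10 | 1.054 | 3.9% | 24.4 | 4% |

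Centre is most likely to be dropped where dropping it costs least. The loss is real but small.

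**3. FAC.** If FAC is not balanced by design, the 95% range of the chance difference between arms in the share of patients at a given level is 1.96 × √(2q(1 − q)/110):
- q = 0.5: ±13 percentage points
- q = 0.2: ±11 percentage points

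The shares q are assumed.

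**4. Predictability, if centre is the sole factor.** Take four centres of 25 and five of 24 (total 220).

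Assignment probability 1: the second patient of each pair is forced.
- 9 × 12 = 108 forced; 108/220 = 49%
- Guessable: (108 + 112 × 0.5)/220 = 164/220 = 74.5%

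Assignment probability below 1: no allocation is certain. Simulation gives the share of allocations made while the centre's counts are unequal. A guesser is right with the assignment probability in those cases, and half the time otherwise.
- 0.9: 0.543 × 0.9 + 0.457 × 0.5 = 72%
- 0.8: 0.606 × 0.8 + 0.394 × 0.5 = 68%
- 0.7: 0.682 × 0.7 + 0.318 × 0.5 = 64% (the simulation itself gives 63%)

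The price of 0.8 is looser balance: in simulation, the mean final difference between arms within a centre rises from 0.4 to 0.8 patients.

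**5. If there are further factors.** With two extra binary factors (assumed) and a guesser who knows only the centre's counts:
- minimised within centre: 74% at probability 1, 67% at 0.8
- minimised across the trial: 68% at probability 1, 61% at 0.8

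**The case against.** **The article is condensed.** The full factor list and the random element are commonly left to the full protocol, and the order of words in Procedure allows minimisation within centre on factors not listed. This stands: silence on these details is not an error, and it is why the predictability point is only conditional. It does not protect the covariate rule. The article does not leave that open; it states a rule, and by that rule the one named design factor can fall out.

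**The loss is small.** This also stands. Omitting centre makes the test conservative, and step 2 shows a few per cent on the standard error at most plausible shares. The case for change rests on its costing nothing.

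**Stronger readings.** A reader might infer three things that the article does not support.
- *Every second allocation is fixed in advance.* This needs centre as sole factor and an assignment probability of 1. Neither is stated.
- *Recruiting staff see the allocations coming.* Allocation is online, and access to the tally is not described. Supervisors were told "the criteria for recruitment of candidates discharged from the inpatient rehabilitation centre", but are not said to recruit. Staff who see both treatments delivered could count allocations; that is plausible but not documented.
- *The plan relies on walking level and time since stroke yet leaves them to chance.* No section treats either as a prognostic factor on which the design depends. The Discussion's remark, "Interestingly, this study found a larger effect size than those that investigated effects in chronic stroke", compares treatment effects between populations. It says nothing about prognosis within this one.

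**Conclusion.** The point holds as an improvement to the analysis model. The only balancing factor named, and the walking level already measured at baseline, should not depend on a significance screen for their place in the model. For centre, omission overstates the standard error by about 1% to 5% if centre explains 2% to 10% of the between-patient variance. Those shares are assumed, as are a 5% screening level and equal allocation. For FAC the gain is precision and adjustment for a chance imbalance of up to about 11 to 13 percentage points; how far FAC predicts the outcome cannot be taken from the article.

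Predictability stands only as a conditional safeguard. The figures of 49% certain and 74% guessable apply if allocation is deterministic on centre alone and staff can count their centre's earlier allocations. The article establishes neither, so no selection bias is shown.

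**What to change.** 1. In Data analysis, replace the significance rule for these variables with a fixed statement: the random coefficients model will include centre (as fixed indicators or as a third level), any other factor used in the minimisation, and baseline FAC, regardless of univariate significance. Cost: one sentence and about ten degrees of freedom if all are fixed (eight for nine centres, two for three FAC levels) out of 220 patients. No new data are needed.

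2. Check the settings of the online procedure. If it is deterministic on centre alone, set an assignment probability of about 0.8. No allocation is then certain, and with centre alone about 68% can be guessed instead of 74%. Cost: a settings change and slightly looser balance within centres. If a random element is already in place, nothing need change here.

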**Figure 1 F1:**
[figure not shown]
**Flow chart**.

### Intervention group

Patients assigned to the intervention group (two participants or more) will receive a 90-minute structured progressive task-oriented CCT programme twice a week over a twelve-week period (24 sessions). The programme includes 4 stages: (1) warming up (5 minutes), (2) circuit class training (60 minutes), (3) evaluation and a short break (10 minutes) and (4) group game (15 minutes). The training programme includes 8 different workstations, intended to improve meaningful tasks related to walking competency, such as balance control, stair walking, turning, transfers and speed walking. The eight workstations incorporated in the circuit are: (1) standing and reaching; (2) stair walking including transfer; (3) walking and picking up various objects from the ground; (4) kicking a ball; (5) stepping up and down; (6) walking course with obstacles; (7) transfers (lying to standing and sitting); and (8) speed walking. Graded progression will be achieved by (1) increasing the difficulty of the task; (2) adding weights; or (3) increasing the number of repetitions. No special (fitness) equipment is needed to perform the tasks. Each workstation will be done for 3 minutes, followed by 3 minutes of rest and 1 minute to change to the next workstation. The participants will complete the exercises in pairs, where one does the exercise while the 'partner' has a rest period and helps the other by keeping track of the number of repetitions and stimulates him/her to perform at their best. Time will be kept by the supervisors. The precise composition of the treatment package for each patient, in terms of appropriate selection of type of workstation, number of repetitions and intensity, will be determined at baseline, based on patients' profiles in terms of muscle strength, physical fitness and mobility status. All patients will keep an activity log in which they record the number of repetitions at each workstation during the sessions, which they will then use as feedback in the next session. The one-hour session of workstation training will be followed by a 15-minute group game, in which the whole group performs a game to improve walking competency. Games will vary across the sessions. Options include a game in which walking tasks are combined with a cognitive task, or a game consisting of fast walking and changing directions. Ball games can of course be used as well, as long as they serve to train walking performance. Incidents that occur during the training sessions (e.g. falls) will be reported by the supervisors to the independent investigator and registered in a falls diary. Patients who are allocated to the intervention group will receive no other physiotherapeutic treatment for the lower extremities.

### Control group

Patients who are allocated to the control group will receive regular care and will therefore be referred to the usual outpatient face-to-face treatment given by physiotherapists at the rehabilitation centres. Treatment designed to improve standing balance control, physical condition and gait performance will be provided. No additional restrictions will be imposed with respect to content, time or duration of the therapy.

### Compliance

In order to conduct this trial uniformly in nine different rehabilitation centres, all supervisors have to be trained in a one-day course before the FIT-Stroke trial starts. In the past year, about 60 physiotherapist and sports therapists have been trained. Each therapist has been informed about: (1) the criteria for recruitment of candidates discharged from the inpatient rehabilitation centre; (2) the aims, design and measurement instruments of the FIT-stroke trial, (3) how to fill in the patients' training diaries, (4) the focus and content of the task-oriented CCT programme and (5) how to stimulate the participants to maintain an active lifestyle after the task-oriented CCT sessions end. After practical training about applying and adapting the eight workstations and how to intensify the workload progressively, all trained supervisors were able to conduct the intervention in a standardized manner. Subsequently, all other physiotherapists, sports therapists and physicians who will be involved in the treatment of the included stroke patients were informed about the content of the intervention by means of presentations in each rehabilitation centre. In order to prevent contamination, therapists were instructed not to change the treatment procedures of the usual face-to-face physiotherapy during the trial. Finally, all managers of rehabilitation centres were asked not to change treatment policies during the FIT-Stroke trial. In the coming years, retraining activities will be organized and an independent investigator ([name]) will monitor on a regular basis whether the content of the task-oriented CCT and the usual physiotherapy are being implemented as intended in the nine rehabilitation centres.

### Outcome measures

The following descriptive variables will be used for the FIT-Stroke Trial: (1) Utrechts Communicatie Onderzoek (UCO). The UCO assesses patients' ability to communicate on a five-point Likert scale, ranging from 'not able to communicate' to 'no communication problems'[28]. (2) Cumulative Illness Rating Scale (CIRS). Co-morbidity will be assessed by the CIRS, which is a valid and reliable instrument that addresses all relevant body systems without using specific diagnoses[29]. (3) Mini Mental State Examination (MMSE). Cognitive functioning will be determined by the MMSE[30]. A score lower than 24 points indicates the presence of cognitive problems[31].

The effect of the intervention will be measured at different outcome levels to determine effectiveness and cost-effectiveness. Primary outcome measure will be the mobility domain of the Stroke Impact Scale (SIS, version 3.0) and the EuroQoL.

#### Stroke Impact Scale (SIS) version 3, Mobility domain

The SIS is a self-reported, stroke-specific measure that includes 59 items and assesses 8 domains related to activities and participation[32]. The mobility domain of the SIS includes 9 questions about patients' perceived competency to keep their balance, to transfer, to walk indoors and climb stairs, to get in and out of a car and to move in their own community. Each item is scored from 'not difficult at all' to 'cannot do it at all' on a 5-point scale. A difference of 10 points on the 'mobility at home and in the community' domain of the SIS is regarded as clinically relevant[33]. SIS has shown excellent clinimetric properties in terms of concurrent and construct validity, test-retest reliability and responsiveness[33,34]. Proxies can also provide valid information on SIS outcome[34]. The SIS has recently been translated into Dutch and the Dutch version showed similar clinimetric properties when re-tested in 27 stroke patients[35]. The SIS will be applied at baseline and 6, 12, 18 and 24 weeks after randomization.

#### EuroQoL

The EuroQol is a generic measure of quality of life (QoL) and consists of a health status profile in five domains (EQ-5D), including two that are directly related to mobility[36]. It also includes a visual analogue scale (VAS) reflecting patients' overall judgement about their current health status. The EuroQol has been validated for use in stroke[37,38]. The advantage of the EuroQol is that it can be transformed into a utility score based on patients' VAS scores and population estimates of the health-status profile, allowing cost-effectiveness assessment. The VAS score will be used to detect possible overall effects of the training programme, compared to usual care, that were not specifically targeted by the intervention programme. For short-term effects, the EuroQol will be assessed at baseline and 6, 12, 18 and 24 weeks after randomization.

